### Eligibility criteria – STICK specific

All STICK participants were required to have a stable estimated glomerular filtration rate (eGFR) of 30–60ml/min/1.73m
^2^ within three months of randomization. Participants were excluded for recent acute kidney Injury (AKI), rapidly declining eGFR
^
25
^, known glomerular disease or current use of non-steroidal anti-inflammatory drugs (NSAID).

### Eligibility criteria – COSIP specific

For COSIP, participants were excluded for known CKD or CVD.

### Randomisation

Once confirmed eligible, participant details were entered into a trial-specific, secure, web-based randomisation service. In STICK, we used a minimization strategy (including previous attendance at a dietitian, diabetes, hypertension and strata of eGFR [30–39, 40–49 and 50–60ml/min/1.73m
^2^]) to support computer-generated block randomization with 1:1 assignment to intervention or usual care. In COSIP, we used computer-generated block randomization to 1:1 assign participants to intervention or usual care. Variable block sizes were used to minimize the occurrence of chance imbalances and to preserve allocation concealment. After confirmation of eligibility, participants may have been randomised in advance to facilitate the scheduling of individuals to attend distinct clinics for either the intervention or usual care arms.

### Study interventions

Usual care: All participants received a one-to-one, dietitian-developed healthy eating guidance session
^
26
^, administered by a trained member of the research team, over 15 minutes following randomization, in addition to written materials emphasizing key messages
^
27
^. Telephone contact was made at months nine and 15 to follow-up on key points on healthy eating (each 15 minutes) with a total contact time of 45 minutes over the course of the trials. Participants randomised to usual care did not meet with the dietitian nor did they receive focused recommendations on sodium intake (other than general guidance contained in 'Health Food for Life'
^
27
^).

Sodium reduction intervention: In addition to healthy eating guidance sessions, those randomised to the intervention received specific counseling on behavioural and environmental factors to promote reduction in sodium intake to a target of <100mmol/day (<2.3g/day). A research dietitian developed the specific components of the intervention, based on the trial of non-pharmacologic interventions in the elderly (TONE) trial
^
28
^. A registered dietitian delivered the intervention using an operations manual to standardize delivery within and across participants. In circumstances where the research dietitian was unavailable, an appropriately trained delegate delivered the intervention. The intervention targeted: (i) reducing use of ‘salt’ during food preparation (encouraging the use of herbs and/or spices); (ii) reducing table ‘salt’ use; (iii) encouraging fresh food consumption over processed or canned foods; (iv) identification of sodium content in foods; (v) modifying the consumption of foods with high sodium content; and (vi) advice on eating outside of home. After determining health literacy, using the Newest Vital Sign UK (NVS-UK)
^
29
^, participants were counselled and behaviour change techniques (goal setting, self-monitoring, frequent contact, feedback and re-enforcement, problem solving and motivational interviewing) were employed to reduce sodium intake by setting specific, measurable, achievable, realistic and timely (SMART) goals for the individual. Tools used included 24-hour dietary recall (analysed using
Nutritics
^
30
^), three-day food diaries and sodium behavior checklists.

The intervention was delivered at all patient contacts up to and including T
_7_ (21 month) visit (
Table 2) with approximately 225–255 minutes of in-person contact and 155 minutes of telephone contact over the course of the trials. Participants had in-person, one-to-one sessions with the study dietitian at randomization (T
_0_), vanguard (T
_V_), where relevant, and T
_2_; group sessions at T
_1 _and T
_4_. In addition, each participant received five separate 15 min telephone calls (Week 1, Week 2, Week 4, Week 6 and Week 10) and 20 min telephone calls at T
_3_, T
_5_, T
_6_ and T
_7_.

**Table 2. T2:** Usual Care and Intervention Sessions.

	Mode	Structure	Duration	Purpose
**Usual Care**				
T _0_ (Randomisation)	In Person	1:1	15 min	Provide Healthy Food for Life booklet and Food Pyramid Poster, set key messages
T _3_ (9 Months)	Phone call	1:1	15 min	Review key messages review progress/changes, troubleshoot
T _5_ (15 Months)	Phone call	1:1	15 min	Review key messages review progress/changes, troubleshoot
**Intervention**				
T _0_ (Randomisation)	In Person	1:1	60 min	Assess diet history, feedback, set SMART goals, fact sheet on salt, food label card
Call 1 (Week 1)	Phone call	1:1	15 min	Review SMART goals, problem solving, review goals
Call 2 (Week 2)	Phone call	1:1	15 min	Review SMART goals, review salt fact sheet, problem solving, review goals
Call 3 (Week 4)	Phone call	1:1	15 min	Review SMART goals, review salt fact sheet, check understanding of high sodium foods, problem solving, review goals
T _V_ (Vanguard) *	In Person	1:1	30 min	Review change from baseline, feedback, review SMART goals
Call 4 (Week 6)	Phone call	1:1	15 min	Review SMART goals, problem solving, review goals
Call 5 (Week 10)	Phone call	1:1	15 min	Review SMART goals, problem solving, review goals
T _1_ (3 Months)	In Person	Group	60 min	Presentation on reducing salt intake, case study discussion, participants identify key take home messages
T _2_ (6 Months)	In Person	1:1	60 min	Review change from baseline (+/- Vanguard), feedback, review SMART goals
T _3_ (9 Months)	Phone Call	1:1	20 min	Review content from T _1_, review SMART goals, review sodium habits, problem solving, review goals
T _4_ (12 Months)	In Person	Group	60 min	Presentation on reading food labels and identifying sodium content in foods, review own food packaging, review food label card
T _5_ (15 Months)	Phone Call	1:1	20 min	Review content from T _4_, review SMART goals, review sodium habits, problem solving, review goals
T _6_ (18 Months)	Phone Call	1:1	20 min	Review SMART goals, review sodium habits, problem solving, review goals
T _7_ (21 Months)	Phone Call	1:1	20 min	Review progress with SMART goals, review sodium habits, problem solving, review goals

* Vanguard visit applicable only for the first 20 participants

### Follow-up schedule

To minimize participant inconvenience and burden, six or seven in-person visits were considered essential (screening, randomization (T
_0_), T
_v_ (first 20 participants for each trial), T
_1_, T
_2_, T
_4_ and T
_8_) and the remaining four follow-up visits were carried out by telephone (T
_3_, T
_5_, T
_6_ and T
_7_) (
Table 3). Post-trial, participants will return to routine clinical care. 

**Table 3. T3:** Schedule of Events.

	T _-1_	T _0_	**T _V_	T _1_	T _2_	T _3_	T _4_	T _5_	T _6_	T _7_	T _8_
	Screening	Time 0	1 Month	3 Months	6 Months	9 Months	12 Months	15 Months	18 Months	21 Months	24 Months
Eligibility Criteria	X										
Informed Consent	X										
Demographics	X	X									X
Medications	X	X	X	X	X	X	X	X	X	X	X
Physical Measurements	X						X				X
Office BP	X		X	X	X		X				X
Abbreviated FFQ	X										X
24-hour ABPM	X										X
eGFR	X	X	X	X			X *				X
Healthy Eating Advice		X				X		X			
Eligibility Check		X									
Randomisation		X									
Medical History		X									
Blood Biochemistry		X	X	X							X
Proteinuria		X					X				X
Biobank Samples		X		X							X
24-hour urine		X	X	X	X		X				X
2 ^nd^ morning fasting urine		X					X				X
In person visits	X	X	X	X	X		X				X
Telephone visit						X		X	X	X	
Adherence and Outcomes			X	X	X	X	X	X	X	X	X

BP=Blood Pressure; FFQ=Food Frequency Questionnaire; ABPM=Ambulatory Blood Pressure Monitor; eGFR=estimated Glomerular Filtration Rate) *STICK participants only; **Vanguard study visit applicable only for the first 20 participants

### Data collection

The following data were collected using standardised case report forms (CRF): demographics, physical measurements (BP, height, weight, waist and hip circumference), medications, medical history, lifestyle factors, randomization allocation, diet, delivery of healthy eating guidance session, delivery of the sodium reduction intervention, clinical events, hospitalisations, adverse events and laboratory results (see extended data
^
24
^). Diet was measured using FFQ, food diaries and a questionnaire focused on sodium-specific behaviours (see extended data
^
24
^). Blood samples were drawn at the time of clinic attendance from participants in the seated position and using a tourniquet. For renin and aldosterone, an EDTA sample was drawn and spun at 2000g for 10minutes at 20 degrees Celsius within 30minutes of phlebotomy. Plasma was then frozen at -20 or -80 degrees Celsius until periodically transferred to our local laboratory using styrofoam boxes and cooler packs to ensure samples did not defrost. Laboratory samples were analysed at the Galway University Hospital laboratory using standardised storage, handling and analytical procedures. We measured serum sodium, potassium, creatinine, glycated haemoglobin (HbA1c), high-density lipoprotein (HDL), low-density lipoprotein (LDL), direct renin, aldosterone, high sensitivity troponin T (hsTnT), Pro B-type Natriuretic Peptide (proBNP), C-reactive protein (CRP), urine protein creatinine ratio (uPCR), 24 hour urine (sodium, potassium, creatinine and protein) and fasting morning urine (sodium, creatinine and protein). This included serum creatinine, measured using methodology traceable to an isotope dilution mass spectrometry (IDMS) reference measurement. Samples were transported to the laboratory within one hour of blood draw and analyses were conducted using standardized laboratory methods on the Roche Cobas® 8000 modular analyser series (Roche Diagnostics Limited, West Sussex, UK), except for HbA1c which was measured using capillary electrophoresis on the Sebia Capillarys 3 automated haemoglobin analyser using the Sebia HbA1c kit (2017/05). After additional consent was obtained, additional blood and urine samples, as well as PAXgene samples for RNA measurement, for biobanking were taken at T
_0_, T
_1_ and T
_8_. To ensure high quality data collection, staff received training on completing paper-based CRF and additional training on entering data into the study database, which included database integrity checks to ensure data consistency.

### Study outcomes

In STICK, the primary outcome measure is change in 24-hour urinary creatinine clearance over two years. We adopt this approach, rather than eGFR, to improve reliability and validity of the primary outcome measure. In COSIP, the primary outcome measure is change in cardiovascular biomarkers (renin, aldosterone, hsTnT, proBNP and CRP) over two years. For COSTICK, the primary outcome measures are creatinine clearance, renin, aldosterone, hsTnT, proBNP and CRP. Secondary outcomes included change in (i) 24 hour ABPM, (ii) 24 hour urine sodium excretion, (iii) 24 hour urine protein, (iv) Modification of Diet in Renal Disease (MDRD) eGFR
^
25
^, (v) Chronic Kidney Disease Epidemiology Collaboration (CKD-EPI) eGFR
^
31
^, (vi) Kidney Disease Improving Global Outcomes (KDIGO) CKD risk category
^
32
^ and (vii) change in PAXgene RNA, and number of (viii) cardiovascular events (acute coronary syndrome, myocardial infarction, heart failure or stroke), (ix) syncope events (prescyncope, syncope, hypotension or orthostatic hypotension) and (x) renal events (acute kidney injury, dialysis, transplant or end stage renal disease).

### Safety reporting

An adverse event is defined as any untoward medical occurrence, including an exacerbation of a pre-existing condition or abnormal laboratory finding, with or without a causal relationship with sodium intake. Participants were monitored for adverse events from informed consent through completion of the final study visit. All adverse events were captured on case report forms, entered into the clinical trial database and coded using the Medical Dictionary for Regulated Activities (MedDRA). Annual line listings of adverse events were reported to the ethics committee.

### Withdrawal of intervention

The study intervention was withdrawn if: (i) symptomatic orthostatic hypotension with systolic BP ≤100mmHg; (ii) diagnosis of glomerular disease (as listed in exclusion criteria); (iii) diagnosis of ESRD, initiation of dialysis or renal transplantation; (iv) prescription of sodium bicarbonate therapy or treating physician recommended against sodium restriction; (v) pregnancy; or (vi) acquired new dietary requirement that precluded the intervention. These participants were encouraged to complete all remaining follow-up visits.

### Sample size calculation

For STICK, we assumed a mean decline in creatinine clearance of 8±5ml/min/1.73m
^2^ over the trial period
^
33
^ and estimated a minimum clinically meaningful effect size of 25% relative reduction. Based on an alpha of 0.05 and power of 80%, a per group sample size of 99 participants was required. Assuming a dropout rate of 5% participants, a net crossover/non-adherence of 5% in favour of the control group, we required a total sample size of 224 participants. For COSIP, we based sample size on the ability to detect an effect size of 0.40 in the between-group difference in mean change scores of biomarkers (80% power and alpha 0.05), equating to a difference of 0.4 of the standard deviation of the change in biomarker. As the COSIP trial is considered exploratory, each biomarker is tested at significance threshold p<0.05. Assuming a dropout rate of 5% participants, a net crossover/non-adherence of 15%, we require a total sample size of 286 participants. Combining COSIP and STICK trials resulted in the ability to detect a smaller effect size.

### Statistical analysis plan

Descriptive statistics will be used to describe baseline characteristics, the flow of trial participants and the amount of missing data for predictor and outcome variables. All losses to follow-up and dropouts will be accounted for and reasons documented. Participants randomised but who did not attend the randomisation visit will be included in analyses. Suitable transformations will be used if the underlying normality assumption is a concern and the bootstrap procedure and a comparison of the median change will be used if a suitable transformation cannot be made. All tests of significance will be two-sided using an alpha of 0.05 for statistical significance and will not be adjusted for multiple testing due to the exploratory nature of the trials. The primary analysis will use the intention-to-treat dataset for all outcomes. A secondary per-protocol analysis will also be carried out, with post randomisation exclusions due to ineligibility, non-compliance, loss to follow-up or missing data.

The primary analysis will consist of fitting a separate linear, multivariable analysis to each of the six outcomes: renin, aldosterone, creatinine clearance, pro-BNP, troponin, and CRP, and secondary outcome measure of 24-hour ABPM. We will review data for implausible values and exclude extreme changes (e.g. change in renin or aldosterone impacted by change in medications). Corresponding baseline measurements of each biomarker will be included as covariates in the model, along with a factor variable for the sub-study in which each patient was recruited, age, sex and whether the participant had attended a dietitian in the 6 months previous to baseline (incident vs prevalent participant). To ensure estimates are more robust to potential effects of missing data at 24-month follow-up, an inverse probability weighting will be applied in all regression analyses to account for the differing propensity of patients with certain baseline characteristics to be included in the final analysis. All covariates included in the regression model will be included in the missingness model, including the other 5 primary endpoints. 

Reporting of primary analysis results will consist of tabulations of the unadjusted and adjusted mean differences at 24 months between intervention and control groups for each biomarker, with confidence intervals of these parameter estimates and p-values, along with descriptive unadjusted mean differences at 24 months between intervention and control groups. A forest plot of the standardised, adjusted mean difference for all 6 endpoints will also be generated. Statistical tests of interaction (Wald) will be used for all subgroup analyses. A sensitivity analysis will be performed to assess the effect of participant reported compliance on treatment effect. Due to the duration of this trial, we expect to have a complete dataset for covariate and outcome data for 90% of participants. Complete case analysis will be used to handle missing data. A sensitivity analysis with multiple imputation will also be carried out if there is >10% missing data for covariates.

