**Inclusion Criteria**		
Age ≥40 years	✓	✓
Average Office BP<160/95mmHg	✓	✓
24hour average from ABPM<150/90mmHg	✓	✓
Anti-hypertensive and/or diuretic medications unchanged for three months	✓	✓
Self-reported willingness to modify dietary intake over sustained period	✓	✓
Written informed consent	✓	✓
Sodium Intake>2.3g/day from FFQ **	✓	✓
Most recent eGFR within 3 months	✓	✗
eGFR 30–60/min/1.73m ^2^ on ≥2 occasions ≥3 months apart	✓	✗

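### The primary analysis is called intention-to-treat, yet it excludes genuine outcome changes, including renin or aldosterone changes that follow a medication change

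*Protocol article*

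**What the plan says.** All of this is in the protocol article, section Statistical analysis plan, unless another section is named.

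- Analysis set: "The primary analysis will use the intention-to-treat dataset for all outcomes".
- Where post-randomisation exclusions belong: a secondary per-protocol analysis, "with post randomisation exclusions due to ineligibility, non-compliance, loss to follow-up or missing data".
- Primary model: "The primary analysis will consist of fitting a separate linear, multivariable analysis to each of the six outcomes", with ABPM added as a secondary outcome.
- Directly after that: "We will review data for implausible values and exclude extreme changes (e.g. change in renin or aldosterone impacted by change in medications").
- Non-normal data: a transformation first; failing that, "the bootstrap procedure and a comparison of the median change will be used if a suitable transformation cannot be made".
- Missing 24-month data: "an inverse probability weighting will be applied in all regression analyses to account for the differing propensity of patients with certain baseline characteristics", and further on, "Complete case analysis will be used to handle missing data".

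Medication stability is an entry condition only (Table 1: "Anti-hypertensive and/or diuretic medications unchanged for three months"). Table 3 has medications recorded at every visit from screening to 24 months, so changes during follow-up are foreseen.

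**The concern.** The exclusion sits in the primary-model paragraph, and its only example is not an error. If a participant's drugs change and renin moves with them, the 24-month value is what happened to that participant after randomisation. Under intention-to-treat it counts.

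The selection need not be balanced between arms. The Introduction cites a trial meta-analysis in which going from moderate to low sodium intake lowered BP by 5.0/2.7 mmHg. A treatment that lowers BP may alter how often antihypertensive or diuretic drugs are changed, and the trials are open-label. Dropping values because of such a change conditions on something that allocation may have caused.

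The two outcomes named are also the ones where it matters most. The Introduction gives activation of the renin-angiotensin-aldosterone system as a main reason for doubt about low sodium intake, and renin and aldosterone are two of the six COSTICK primary outcomes.

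**Working it through.** **1. The passages side by side.** Primary analysis: intention-to-treat, all outcomes. Post-randomisation exclusions: per-protocol, secondary. Primary-model paragraph: exclude extreme changes, for example those affected by medication. The third statement cannot be carried out together with the first two. The sentence has two parts, a review for implausible values and an exclusion of extreme changes. The first is ordinary data cleaning. The second, by its own example, is not.

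**2. Do other provisions bring the values back?** The weighting is described for baseline characteristics, so it does not clearly address loss caused by a post-randomisation event or by the outcome itself. The stated sensitivity analyses concern reported compliance and multiple imputation for missing covariates. Neither restores the excluded values.

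**3. The design effect used below.** STICK: 25% of a decline of 8 is 2, and 2/5 = 0.40 SD. COSIP: 0.40 SD as stated. Check: n = 2(1.960 + 0.842)²/0.40² = 2 × 7.849/0.16 = 98.1, or 99 per group with the t correction, as the article gives for STICK. The planned totals are 224 + 286 = 510. With 5% dropout this is 510 × 0.95/2 = 242 per arm, so 240 is used for the pooled analysis.

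**4. Exclusion by size (cut-offs assumed; the article gives none).** Put the arms at −0.2 and +0.2 with SD 1. The pooled SD is √(1 + 0.04) = 1.0198, and values beyond c = k × 1.0198 are dropped. The kept mean in the upper arm is

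0.2 + [φ(c + 0.2) − φ(c − 0.2)] / [Φ(c − 0.2) − Φ(−c − 0.2)],

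and by symmetry the estimated difference is twice that.

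- k = 2: 0.2 + (0.03249 − 0.07346)/(0.96709 − 0.01256) = 0.1571, so the difference is 0.314.
- k = 2.5: 0.2 + (0.00911 − 0.02525)/(0.99060 − 0.00298) = 0.1837, so 0.367.
- k = 3: 0.2 + (0.00197 − 0.00669)/(0.99788 − 0.00056) = 0.1953, so 0.391.

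Simulation with the cut-off estimated from the data agrees:

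| Cut-off | Estimate (true 0.40) | Attenuation | Coverage, 240 per arm | Coverage, 143 per arm |
|---|---|---|---|---|
| 2 SD | 0.31 to 0.32 | about 21% | about 82% | about 87% |
| 2.5 SD | 0.37 | about 8% | about 93% | about 93% |
| 3 SD | 0.39 | about 2% | about 95% | about 95% |

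The 143 per arm is COSIP alone (286/2). With heavy-tailed changes (t with 4 df) and a 2 SD cut-off, the estimate is about 0.345 and coverage about 88% at 240 per arm. With a true difference of 0 the estimate stays at 0 and coverage at about 95% for all three cut-offs.

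**5. Exclusion for medication change (all inputs assumed).** Let 20% of controls change medication because BP is high, so the threshold is t = 0.842. Let the intervention lower BP by s SD, and let the BP residual and the biomarker change correlate at ρ. With λ(x) = φ(x)/Φ(x), the bias is ρ[λ(t) − λ(t + s)]. Here λ(t) = 0.350, λ(t + 0.3) = 0.238 and λ(t + 0.5) = 0.178.

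- ρ = 0.3: 0.3 × 0.112 = 0.034 SD (s = 0.3); 0.3 × 0.172 = 0.052 SD (s = 0.5).
- ρ = 0.5: 0.5 × 0.112 = 0.056 SD (s = 0.3); 0.5 × 0.172 = 0.086 SD (s = 0.5).

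Exclusions are 20% in control against 12.7% (s = 0.3) or 9.0% (s = 0.5) in intervention. This bias is present when the true effect is 0. Its sign follows ρ: a negative correlation reverses it. A different assumption, with 15% and 35% changing medication in the two arms, gave about −0.05 SD under the null.

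**The case against.** The strongest reply is that the sentence is meant narrowly, as a screen for implausible values plus removal of renin and aldosterone results confounded by drugs. The article already has a transformation and bootstrap route for skewed data, so trimming is not its planned answer to long tails. This has force. A reader might infer that large renin or aldosterone rises will be deleted simply because they are large. The text permits that but does not say it. The narrow reading still leaves the medication example, which is the part that conflicts with intention-to-treat.

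Other objections stand in part:

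- The sentence excludes changes, and each biomarker has its own model. A reader might infer that whole participants are removed; the text does not say so. In that biomarker's complete-case model, however, the effect is the same.
- The absence of a cut-off is not a fault here. It may be in a statistical analysis plan that is not shown. A cut-off would reduce discretion but would not resolve the contradiction.
- The Discussion promises blinded outcome assessment, including a blinded statistician. That limits selection made with knowledge of the arm. It does not remove bias from a rule that depends on the outcome or on a consequence of treatment.
- A 2 SD cut-off is a severe meaning of extreme, and at 3 SD little is lost. The 0.40 effect is also large for the pooled sample, since the article says pooling allows a smaller effect to be detected. If standardised differences use the trimmed SD, attenuation need not appear at all: about 0.355 for normal data at 2 SD, but about 0.46 for heavy-tailed data.
- The trials are exploratory, and the example touches two of six primary outcomes. This tempers the consequence but does not make the statements compatible.

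**Conclusion.** Wrong as written. The primary analysis cannot be intention-to-treat for all outcomes and also exclude genuine changes because medication changed or because the change was extreme.

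The supported conclusion is that the rule can bias the comparison, not that it will, and not by a known amount. Medication-related exclusion can push the estimate either way, even with no true effect; under the assumed scenarios the shift is within about 0.1 SD. Exclusion by size is neutral under an exact null and can attenuate a real effect, from about 2% at 3 SD to about 21% at 2 SD for normal data. The cut-offs, medication-change rates and correlations are all assumptions. A claim of serious under-coverage in general would go too far, since it rests on the 2 SD cut-off. The contradiction in the text depends on none of these figures.

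**What to change.** The article reports that final visits are complete and cleaning is under way ahead of database lock, so the wording can still be changed. Replace the exclusion sentence with text to this effect:

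*All genuine measured values are kept in the primary intention-to-treat analysis, whatever the size of the change and whether or not medication changed. A value is removed only for a documented laboratory, collection or recording error, judged blind to allocation before database lock. Extreme values are handled by the transformation, or the bootstrap and median comparison, already planned. An analysis excluding medication-affected or extreme changes is reported as a sensitivity analysis, with the number excluded shown by arm and by biomarker.*

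No new data are needed. The cost is somewhat wider intervals than after exclusion. Readers who want the result without medication-affected values still get it, under its proper label.

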Our trials have a number of limitations. First, the trials are open-label as it wasn’t practical to blind participants, investigators or study staff to the intervention. However, to minimize the risk of bias we will perform blinded outcome assessment including blinding of the trial statistician. Second, participants in the usual care arm may receive non-study recommendations on sodium reduction, reducing the likelihood of observing the effect from our intervention, biasing toward the null. To minimise this risk of bias, treating clinicians were asked not to explicitly discuss sodium reduction with participants unless strongly indicated and the trial intervention was to be withdrawn. Similarly, as contamination is a threat to trial validity, only participants randomized to the intervention met with the study dietitian, participants were instructed not to discuss the educational sessions with other participants and participants were invited to attend follow-up visits on days based on study allocation. Third, there is a risk of volunteer bias, as participants may differ from non-participants, impacting trial generalizability. We will measure the potential effect of this bias by comparing non-participants and participants. Fourth, the primary outcome measures are changes in biomarkers rather than hard clinical endpoints, which would require a trial of longer duration (to accumulate a sufficient number of clinical events) to demonstrate a treatment effect. The findings of our trials can be used to inform future, larger, multicenter trials. Fifth, individuals with CKD may have previously consulted with a dietitian and received advice on lowering sodium intake, limiting their ‘responsiveness’ to our intervention. Therefore, we included previous dietitian review in the minimization strategy for randomization in STICK; in addition, we believe that the trial intervention is more intensive than standard care. Finally, there is a risk of non-compliance with the intervention and a reliance on participant self-reported adherence as this is a behavioural intervention trial. To maximise compliance, we: (i) self-selected participants most likely to adhere to a behavioural intervention; (ii) implemented standardised telephone follow-up to provide additional advice and support, answer questions, reinforce key messages and remind participants about visits; and (iii) provided written materials on the study interventions. We also completed multiple 24-hour urine collections for sodium to measure objectively measure adherence, although these collections also have limitations

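### The primary COSTICK model omits three of the four STICK minimisation factors and words the fourth inconsistently; the likely cost is some precision, not validity

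*Protocol article*

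**What the plan says.** **Allocation.** The Randomisation section of the protocol article says that STICK used a minimisation strategy, "including previous attendance at a dietitian, diabetes, hypertension and strata of eGFR", with eGFR strata 30–39, 40–49 and 50–60. COSIP had no such factors: "In COSIP, we used computer-generated block randomization to 1:1 assign participants to intervention or usual care". The Discussion confirms the dietitian factor: "we included previous dietitian review in the minimization strategy for randomization in STICK". Neither place gives a look-back period.

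**Analysis.** The Statistical analysis plan section fits one linear model per outcome and itemises the covariates. The first is the outcome's own starting value: "Corresponding baseline measurements of each biomarker will be included as covariates in the model". The others follow in a single phrase: "along with a factor variable for the sub-study in which each patient was recruited, age, sex and whether the participant had attended a dietitian". That last item is then given a time window: "in the 6 months previous to baseline (incident vs prevalent participant". Diabetes, hypertension and eGFR stratum are not on the list, and no reason is given. The same section fills the missingness model from the regression covariates plus the other five primary endpoints, so the three factors are absent from the inverse probability weights too.

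**Scope.** The sub-study term shows that this is the pooled model, and the Abstract says that the primary report covers both trial populations. The article describes no STICK-only model.

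**The concern.** Minimisation forces the arms to be alike on the chosen factors, so the treatment estimate varies less from one possible allocation to the next than under simple randomisation. A regression that leaves the factors out still counts the variation they explain as noise. Where they are prognostic, its standard error is larger than the true sampling variability: confidence intervals are too wide, the test rejects less often than its nominal 5%, and the benefit of balancing is partly thrown away.

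The investigators chose these factors as worth balancing, and one of them is kidney function, in a programme where creatinine clearance is a primary outcome. For renin, aldosterone, hsTnT, proBNP and CRP, the only kidney-function term in the model is the binary sub-study factor. The list keeps one minimisation factor and adds age and sex, which were not minimised on. It is therefore a specified model that departs from the allocation scheme, not a detail left open.

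**Working it through.** **1. The plan's own sample sizes.** From the Sample size calculation section: "we assumed a mean decline in creatinine clearance of 8±5ml/min/1.73m"², and a 25% relative reduction, so the difference is 0.25 × 8 = 2, or 2/5 = 0.4 SD. With two-sided alpha 0.05 and 80% power, n per group = 2 × (1.960 + 0.842)² × 5²/2² = 98.1, rounded up to 99 as stated. For the STICK total, 198/0.95/0.95 = 219 and 196.2/0.95/0.95² = 229; the stated 224 lies between. For COSIP, 196.2/0.95/0.85² = 286, as stated. The planned total is 224 + 286 = 510, of whom 224 (44%) were minimised.

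**2. Analysed numbers.** The plan expects complete data for 90%: about 202 in STICK and 257 in COSIP, 459 in all. STICK's share is w = 202/459 = 0.44.

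**3. Formula.** Let R² be the share of the outcome variance left after the planned covariates that diabetes, hypertension and eGFR stratum explain. The documents give no value, so 2%, 10% and 30% are **assumed**. With near-perfect balance, and with the added terms acting among STICK participants only:

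- STICK alone: SE ratio (factors in / factors out) = √(1 − R²)
- Pooled: SE ratio = √(1 − w·R²)
- True size of the nominal 5% test when the factors are omitted = 2 × [1 − Φ(1.96 / SE ratio)]

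| Assumed R² | STICK alone: SE cut; size if omitted | Pooled: SE cut; size if omitted |
|---|---|---|
| 2% | 1.0%; 4.8% | 0.4%; 4.9% |
| 10% | 5.1%; 3.9% | 2.2%; 4.5% |
| 30% | 16.3%; 1.9% | 6.8%; 3.5% |

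**4. Simulation.** This drops the perfect-balance assumption. STICK was minimised on its four factors with an assumed 80% biased coin, and COSIP was block-randomised. Linear models were fitted with and without the three factors, with 2,500 null and 2,000 alternative runs per setting. The Monte Carlo error on type I error is √(0.05 × 0.95/2500) = 0.4 points. Power is at 0.4 SD for STICK and 0.26 SD for the pooled model.

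| Setting | R² | Mean SE, out → in | SE cut | Type I error, out / in | Power, out / in |
|---|---|---|---|---|---|
| STICK | 2% | 0.1406 → 0.1393 | 0.9% | 5.3% / 5.6% | 82% / 82% |
| STICK | 10% | 0.1407 → 0.1335 | 5.1% | 3.9% / 5.0% | 83% / 85% |
| STICK | 30% | 0.1411 → 0.1181 | 16.3% | 1.8% / 5.0% | 85% / 93% |
| Pooled | 2% | 0.0935 → 0.0931 | 0.4% | 4.9% / 4.9% | 81% / 81% |
| Pooled | 10% | 0.0933 → 0.0913 | 2.1% | 4.2% / 4.8% | 81% / 82% |
| Pooled | 30% | 0.0934 → 0.0871 | 6.7% | 4.0% / 5.4% | 83% / 86% |

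The SE reductions agree with the formula. The pooled type I errors sit within about one Monte Carlo error of it. One further pooled setting (R² 5%) gave 6.0% with the factors omitted and 6.3% with them included. The fuller model is the higher of the two, so the omission does not explain the excess; I read it as simulation noise.

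**5. Limits.** Assumed STICK prevalences were 30% prior dietitian contact, 25% diabetes and 70% hypertension, with equal eGFR strata. The inverse probability weighting was not simulated. In the pooled runs diabetes and hypertension were entered for STICK participants only. Entering them for COSIP too could gain more if they are prognostic there.

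**The case against.** The strongest reply is that this matters little for the analysis actually specified. Only 224 of 510 planned participants were minimised, so a reader who carried STICK-only figures over to the pooled model would overstate the effect: at R² 10% the SE cut is about 2%, not 5%, and power moves by one point. This stands.

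The upper R² values may also be generous. Each model already holds the outcome's own baseline, sub-study, age and sex. Baseline creatinine clearance probably carries much of the eGFR-stratum information for that outcome. This is less clear for the other five biomarkers, but no figure in the documents supports a large R².

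Three stronger readings are tempting and fail:

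- *The tests are invalid or biased.* The omission errs on the safe side. It biases nothing, and no false-positive inflation attributable to it appeared.
- *The trials are underpowered because of it.* The planned 99 per group assumes no covariate adjustment, and simulated STICK power with the factors omitted stayed at 82% to 85% (crossover not modelled). What is lost is extra efficiency, not the planned power.
- *The dietitian factor was redefined after allocation.* Two sections give no window and one gives six months. That is compatible with one variable described briefly and then fully. The documents show inconsistent wording, not a change.

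**Conclusion.** The point holds as a modest one. Three of the four STICK minimisation factors are missing from an itemised primary model without explanation, and the dietitian covariate carries a six-month window that the allocation text lacks. If the missing factors are prognostic beyond the existing covariates, standard errors are too large and the test is conservative.

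In the pooled primary model the effect is small unless the factors are strongly prognostic: type I error stays at about 4% to 5% across the three assumed R² values. In a STICK-only analysis it could matter more, with type I error falling to about 2% at the highest value.

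These sizes rest on the assumed R², the assumed biased coin and prevalences, and unweighted models. The discrepancy between the two sections does not depend on those assumptions. The case for acting is that the correction is nearly free and, by the Study status section, database lock and analysis are still ahead.

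**What to change.** Before database lock, amend the primary model as follows.

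1. Add diabetes, hypertension and eGFR stratum, using the values entered at randomisation. In the pooled model, replace the two-level sub-study term with a four-level factor: STICK 30–39, STICK 40–49, STICK 50–60, and COSIP. For COSIP, which had no minimisation entries, take diabetes and hypertension from the baseline medical history scheduled in Table 3, or state that these terms apply to STICK only.
2. Use the dietitian variable as held in the STICK minimisation system, say how the COSIP value is defined, and reconcile the wording in the Randomisation, Statistical analysis plan and Discussion sections.
3. Under the plan's existing rule, the added covariates then also enter the missingness model; confirm this in the text.

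If a factor is to stay out, give the reason.

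The cost is a sentence or two and four extra model terms (two for eGFR strata, one each for diabetes and hypertension), against about 459 analysed participants. No new data are needed.
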